#### Secondary Outcomes

The secondary outcomes will include the duration until the occurrence of the first seizure, the severity of seizures, the safety and tolerance of the medication, and the overall stroke outcome. During the 18-month follow-up, we will record mortality, medication safety, and tolerability data at each visit. Stroke outcome will be measured using the modified Rankin scale at 3 and 18 months (Table 1 and Figure 2).

### Statistical Analysis

Continuous variables will be assessed using a 2-tailed *t* test or ANOVA, followed by the Fisher least significant difference test. When data are not normally distributed, analyses will be performed using the nonparametric ANOVA Kruskal-Wallis H test followed by Dunn multiple comparison test for nonrepeated measures and the Friedman test for repeated measures. ANOVA will be used where sessions or quadrants will be treated as a within-subject factor and groups as a between-subjects factor. Analyses will be performed using a chi-square test, Yates chi-square test, or Fisher exact test for nominal variables. Differences will be considered statistically significant at a *P* value <.05, and actual *P* value will be reported, unless *P*<.001.

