## Introduction

### Background

Advances in stroke treatment have caused a considerable reduction in stroke mortality; however, the number of stroke survivors living with disability has increased significantly. Seizures and epilepsy related to ischemic stroke are common, and poststroke epilepsy is a significant clinical problem for stroke survivors. Stroke is the most common cause of epilepsy in older adults and for patients older than 65 years of age, and poststroke epilepsy accounts for 30%-50% of new-onset seizures [1]. The incidence of early seizures (occurring within the first 1-2 weeks of stroke) is 2.4%-5.4%, and the risk of poststroke late seizures (seizures occurring later than after 14 days of stroke) is approximately 7%-18% [1,2]. Late-onset poststroke epilepsy has a higher recurrence rate of up to 71.5% within 10 years after stroke [3]. Our previous study demonstrated that seizures during stroke increase overall morbidity and mortality [4]. The stroke severity, location (for example, middle cerebral artery [MCA] infarcts in our study), and the type of pathological changes, genetic factors, and pre- and postinjury exposure to nongenetic factors influence the susceptibility of patients with ischemic stroke [5,6]. The standardized morbidity rate of developing epilepsy is highest during the first year after stroke. In addition, higher National Institutes of Health Stroke Scale (NIHSS) score [7], cortical involvement, younger age, and central nervous system morbidities are associated with higher risk of poststroke epilepsy [1,8].

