## Methods

### Overview

We will conduct a prospective randomized, triple-blind, and placebo-controlled study. To calculate the appropriate sample size, we took into account various factors including the population size, margin of error, confidence level, expected variance, number of patients with MCA infarcts admitted to our medical center annually, and potential loss rate. We used G*Power software (Heinrich-Heine-Universität Düsseldorf) to perform these calculations. Specifically, we used an effect size ranging from 0.25 to 0.4, α error probability of .05, power of 0.5, 3 groups, 2 measurements, and a correlation of 0.05 between repeated measures. The resulting total sample size ranged from 51 to 120. Based on the potential number of patients admitted to our medical center and the expected loss rate, we estimated that enrolling 180 cases would be reasonable.

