### Procedure and Assessment

We will document patients with initial NIHSS scores of >8 [40]. For reperfusion therapy, we will also use a modified Rankin scale for treatment evaluation [43]. For each participant, we will use brain MRI to confirm MCA territory infarction and exclude that of other territories and lacunar infarction. The MRI image depicting the typical case with an MCA infarct enrolled in this study is displayed in Figure 3. Baseline EEG during admission prior to AED administration will be arranged to exclude patients with early or concurrent clinical or electrographic seizures (Figure 2).

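### The rule for non-normal repeated data leads, by inference, to a Friedman test for the modified Rankin score, and that test cannot compare the arms

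*Protocol article*

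**What the plan says.** The Statistical Analysis section of the protocol article assigns tests by type of data and not by outcome. Non-normal data go to the "nonparametric ANOVA Kruskal-Wallis H test", "followed by Dunn multiple comparison test for nonrepeated measures and the Friedman test for repeated measures". The next sentence adds a parametric option: "ANOVA will be used where sessions or quadrants will be treated as a within-subject factor and groups as a between-subjects factor". Nominal variables get chi-square or Fisher tests. No test is tied to the modified Rankin score, and none carries a covariate.

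Under Secondary Outcomes, "Stroke outcome will be measured using the modified Rankin scale at 3 and 18 months"; the Abstract gives the same two times. Table 1 differs: it ticks the score within 3 days and at 18 months, with nothing at 3 months.

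On baseline severity, Procedure and Assessment says "We will document patients with initial NIHSS scores of >8", and Table 1 records NIHSS at entry. The Background lists a higher NIHSS among factors that "are associated with higher risk of poststroke epilepsy". It does not relate NIHSS to the Rankin score.

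**The concern.** The Rankin score is the trial's measure of functional outcome. The Introduction cites reports that prophylactic antiepileptic drugs may go with worse outcomes, so this comparison bears on harm as well as benefit. The question is whether the arms differ.

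The Friedman test answers another question: whether scores differ between visits within the same patients. Run on all patients, it ignores arm. Run separately in each arm, it yields three tests of change over time, and a reader may take a significant result in one arm and not in another as a treatment difference. If an analyst followed the stated rule for this score, the functional comparison could miss a real difference or present ordinary recovery as a finding.

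**Working it through.** **The plan's own figure.** The article gives none for the Rankin comparison. Taken from the article: 180 planned participants (60 per arm if equal), "α error probability of .05", three arms, and visits at 3 and 18 months.

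**Step 1: which listed test applies.** The Rankin score is an ordered scale with few levels, so the normal-theory branch does not fit it. Set against the stated rules:

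| Listed test | Compares arms? | Fit to the score at two visits |
|---|---|---|
| Friedman | No | The only nonparametric test given for repeated data |
| Kruskal-Wallis, then Dunn | Yes | Valid at one visit, but reserved for nonrepeated measures |
| ANOVA with within- and between-subject factors | Yes | Parametric; its within-subject factor is worded for sessions or quadrants, which this trial does not have |

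**Step 2: what Friedman responds to.** With two visits it reduces to a sign test. If *a* patients have the higher score at the first visit and *c* at the second, the statistic is (a − c)² / (a + c), referred to chi-square on 1 degree of freedom. Adding the same amount to both of a patient's scores leaves *a* and *c* unchanged, so a constant arm difference drops out.

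**Step 3: size.** Assumptions, not from the article: a seven-level score cut from a normal latent variable; between-visit latent correlation 0.8; both drugs shifted by the same latent amount at both post-randomisation visits; all 180 patients analysed. Each row uses 5,000 simulated trials.

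| Improvement between visits (SD) | Drug shift (SD) | Pooled Friedman rejects | Three per-arm Friedman verdicts disagree |
|---|---|---|---|
| 0 | 0 | 5.3% | 13.7% |
| 0 | 0.5 | 4.8% | 13.9% |
| 0.15 | 0 | 73.7% | 66.1% |
| 0.2 | 0 | 94.0% | 74.4% |
| 0.3 | 0 | 99.9% | 37.2% |
| 0.3 | 0.5 | 99.9% | 38.0% |

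The drug shift hardly moves the rejection rate; the time trend drives it. A 1.0 SD shift with no trend also gave 5%. Kruskal-Wallis at 18 months had about 76-79% power for the 0.5 SD shift.

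**Step 4: what adjustment for NIHSS could add.** The article gives no correlation *r* between NIHSS and the later score, so r = 0.3 to 0.6 is assumed. For a continuous outcome the residual variance is multiplied by 1 − r². Pairwise two-sided power for a 0.5 SD difference with 60 per arm is Φ(0.5 × √30 / √(1 − r²) − 1.96), with 0.5 × √30 = 2.739.

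| r | 1 − r² | Variance removed | Power |
|---|---|---|---|
| 0 | 1.00 | 0% | Φ(0.779) = 0.78 |
| 0.3 | 0.91 | 9% | Φ(0.911) = 0.82 |
| 0.5 | 0.75 | 25% | Φ(1.202) = 0.89 |
| 0.6 | 0.64 | 36% | Φ(1.463) = 0.93 |

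These values are for a continuous outcome, not for a proportional-odds model. Entry requires NIHSS above 8, and a truncated range tends to weaken a correlation, so the gain may be smaller.

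**The case against.** The strongest reply is that nothing in the article sends the Rankin score to Friedman. The outcome can be read as two separate endpoints, one at 3 months and one at 18. Each would then be a nonrepeated three-arm comparison, for which Kruskal-Wallis with Dunn is listed and valid. The ANOVA in the next sentence also has a group factor. This stands in part: the Friedman route is an inference, and a reader should not conclude that the article prescribes it for this score or lists no arm comparison at all. What remains is that the only nonparametric rule for repeated data cannot answer the trial's question, and the article does not say which listed test does.

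A reader might also infer that leaving out NIHSS is a mistake, or that NIHSS is known here to predict the Rankin score strongly. The document supports neither. It links NIHSS to epilepsy only. Under randomisation the unadjusted tests are valid; their simulated type I error was 4.6-5.3%. Covariates may also be set in an analysis plan that is not shown.

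Finally, the simulated shift applies to two visits after randomisation. If the repeated pair were baseline and 18 months, as in Table 1, a drug effect would arise only at the second visit and Friedman would not be wholly blind to it. It would still merge that effect with recovery and could not attribute it to an arm.

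**Conclusion.** The point holds in a limited form. The stated rule for non-normal repeated data names a test without an arm term, and the Rankin score falls under that rule by inference. Applied to scores at 3 and 18 months, the test rejects at about its 5% null rate for a constant arm difference, and almost always for a 0.3 SD improvement shared by all arms. Those rates rest on the assumed latent model, but the insensitivity to a constant shift follows from the ranking itself.

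Adjustment for NIHSS is a separate, optional gain: about 9%-36% less residual variance if r is 0.3-0.6, possibly less. Its absence is not an error.

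This concerns a secondary outcome and leaves the primary comparison untouched. The change is worth making because the outcome bears on harm and the cost is small.

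**What to change.** Remove Friedman as a between-arm test for the modified Rankin score. Specify a proportional-odds model with arm as the factor, fitted at 3 months and at 18 months, reporting the odds ratio with confidence interval for each drug against placebo. Count death as category 6; deaths are already recorded at the follow-up visits. Include baseline NIHSS, already collected at entry, as a covariate. This also removes the choice of test by normality for this outcome.

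The model gives four odds ratios (two drugs at two times), so say how they will be read together.

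Reconcile Table 1 with Secondary Outcomes, since the table shows no 3-month Rankin assessment.

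Cost: a change of analysis wording and a proportional-odds assumption to check. No new data are needed if the 3-month score is being taken as Secondary Outcomes states.

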### Ethical Considerations

This study received approval from the institutional review board (IRB) at National Cheng Kung University Hospital (A-BR-108-107). Each participant and their families were provided with a comprehensive verbal explanation of the study and were asked to provide informed consent, as authorized by the IRB. Participants completed their signatures on the consent forms to indicate their agreement to participate in the study.

The study data would be kept anonymous and deidentified to protect the participants’ privacy. Participants were not offered any form of compensation or reimbursement for their involvement in this human subjects’ research.

## Results

Participant recruitment began on August 1, 2020 in National Cheng Kung University Hospital. Intervention, postintervention, and follow-up observation are still ongoing for the participants. The study is projected to be completed by January 31, 2025.

## Discussion

### Principal Findings

Although reports have not supported the role of prophylactic AEDs in the prevention of poststroke seizure because of a lack of randomized control trials, a lack of detected early clinical biomarkers, and worse outcomes with traditional AEDs, we will document the potential prophylactic effect of LEV and PER on poststroke seizures and epilepsy in patients with MCA infarct in this randomized clinical trial and determine the antiepileptogenic potential of LEV and PER in patients with major ischemic stroke in terms of seizure frequency and severity. We will also evaluate the safety and tolerability of these prophylactic treatments. This study will influence both stroke and epilepsy care considerably, including by potentially reducing long-term care costs and enhancing the quality of life of stroke survivors.

In addition to LEV, previous studies, including our own, have identified PER as a new AED with potential antiepileptogenic properties, attributed to its unique postsynaptic AMPA antagonism [32,38,39]. While it is not yet approved as a first-line treatment for focal epilepsy in many countries, this medication has potential and could be used at an early stage if our study confirms its effectiveness in prophylaxis against poststroke epilepsy.

The administration of AED or placebo for a period of 3 months is intended to intervene in the epileptogenesis phase, based on the relative duration of this phase observed in animal studies. Typically, the epileptogenesis phase in animal studies lasts for around 1 week, although this can vary depending on the animal model of seizure and epilepsy following brain injuries. By extrapolating from rat studies to human years [44], it is estimated that the epileptogenesis phase in rats is similar to around 3-4 months of human life. For the purposes of clinical feasibility, we administer a 3-month duration of AED.

In our trial to provide prophylactic treatment for epilepsy in patients who have not yet experienced seizures and are relatively vulnerable, particularly older patients who have endured stroke with multiple comorbidities, such as renal and liver diseases, we have opted for a relatively low medication dosage. Regarding the inclusion criteria, we do not enroll patients with severe renal or hepatic failure. However, we include patients who are already undergoing dialysis treatment. We assess the severity of liver disease using the Child-Pugh classification, with grade C being categorized as severe liver disease [45]. For the evaluation of renal disease severity, we use the National Kidney Foundation criteria, classifying stage 4 and above as severe renal disease [46]. In accordance with the renal dose adjustments for LEV [47], dosages vary depending on the level of renal impairment. For patients with mild renal impairment (glomerular filtration rate [GFR] 60-89 mL/min/1.73 m^2^), the recommended dosage range is 1000-2000 mg per day. For those with moderate renal impairment (GFR 30-59 mL/min/1.73 m^2^), the dose ranges from 500 to 1500 mg per day, while patients with severe renal impairment (GFR 15-29 mL/min/1.73 m^2^) are prescribed doses of 500-1000 mg per day. For individuals undergoing hemodialysis, the recommended dosage is 500-1000 mg per day with an additional 250-500 mg postdialysis supplement.

Our decision regarding medication dosages is guided by the World Health Organization’s Defined Daily Dose (DDD) guidelines [48] and our collective clinical experience. The DDD represents the estimated average daily maintenance dose for a drug when used for its primary indication in adults, taking into account our clinical expertise. For PER, the DDD is 8 mg, while for LEV, it is 1500 mg. In our study, we have chosen to administer PER at a dosage of 4 mg and LEV at 1000 mg. For LEV, this choice is driven by the fact that the majority of our recruited patients have normal renal function, with only a relatively small subset experiencing renal impairment (mild, moderate, or hemodialysis). To ensure randomization and maintain blinding in our triple-blind study, we have opted for a lower dose of 1000 mg per day. Of note, our blinding design excludes the use of postdialysis supplemental dosing.

According to the existing literature, late-onset seizures following a stroke typically exhibit a peak incidence between 6 and 12 months after the initial event [1]. Studies have shown that after an ischemic stroke, the highest risk for the occurrence of the first unprovoked poststroke seizure is observed during the initial follow-up year [5,49]. Furthermore, another study has reported the annual event risk of seizures after the first-ever ischemic stroke, indicating a risk of 6.3% after 1 year, 2.4% after 2 years, 1.3% after 3 years, and 0.3% thereafter [50]. Although the annual risk of seizures may indeed increase in subsequent years, given the highest risk observed during the first year and considering the practical feasibility of our protocol, we have chosen an 18-month follow-up period at this stage.

In terms of stroke severity, minor strokes (those with a small lesion size) are less likely to lead to the development of poststroke epilepsy. For each patient, we routinely arrange for MRI scans as a standard imaging procedure to assess the stroke, including its size, location, and the presence or absence of hemorrhagic transformation during admission. We do not typically perform brain computed tomography (CT) scans. It is worth noting that the absence of hemorrhagic transformation at the onset of the stroke does not eliminate the possibility of it occurring later during the acute stage. In the event of acute deterioration in neurological symptoms and signs, we arrange for follow-up brain MRI or CT scans and provide standard care.

In our protocol, we initiate treatment for patients with PLEDs. PLEDs have been considered to have a high association with seizures [51,52], and among the epileptiform abnormalities, the presence of lateralized periodic discharges was associated with a significantly increased risk of seizure [53]. In addition, PLEDs were associated with an acute process and occurred early during the course of the illness, with stroke being the main etiology [52].

While patients and research teams remain blinded to the allocated medications, the medication list, including cytochrome P450 inducers or inhibitors, is made available to study participants. This allows for vigilance regarding any potential drug-drug interactions. Moreover, given that our study involves a randomized controlled trial with blinding, which necessitates careful control over factors like color, size, and quantity of both the active drug and placebo tablets, the use of a powdered form is the most practical approach for conducting this trial. It is worth noting that the oral suspension form is only available for one of the medications, and furthermore, these oral suspension forms come in different colors. Additionally, the cost associated with preparing a placebo suspension in this context is prohibitively high. Regarding the issue of bioavailability, there has been no direct comparative study on bioavailability between the tablet and powdered forms. We do have clinical experience using the powdered form for patients who face challenges swallowing tablets or those reliant on nasogastric tubes. This practice is consistent with the medication package insert instructions. With their availability in multiple formulations in the future, these AEDs could serve as a potential drug for epilepsy prophylaxis during epileptogenesis.

### Conclusions

We anticipate that the intervention group will experience a lower incidence and severity of poststroke epilepsy than the control group. We will be able to document the potential prophylactic effect of LEV and PER in poststroke seizures and epilepsy in patients with MCA infarct and determine the antiepileptogenetic potential of LEV and PER in patients with major ischemic stroke.

## Abbreviations

AED: antiepileptic drug
AMPA: alpha-amino-3-hydroxy-5-methyl-4-isoxazolepropionic acid
CT: computed tomography
DDD: Defined Daily Dose
EEG: electroencephalogram
GABA: gamma-aminobutyric acid
GFR: glomerular filtration rate
IRB: institutional review board
LEV: levetiracetam
MCA: middle cerebral artery
MRI: magnetic resonance imaging
NIHSS: National Institutes of Health Stroke Scale
PER: perampanel
PLED: periodic lateralized epileptiform discharge
